### 2.10. Ethics and dissemination

Ethical approval for this study (2022BZYLL0402) was provided by the Ethics Committee of the Beijing University of Chinese Medicine, Beijing, on April 28, 2022. Written informed consent was obtained from all participants before enrollment in the study. The results will be published in a peer-reviewed journal and disseminated electronically and in print regardless of the results.

### 2.11. Data and safety monitoring boards

According to the operation guide for the establishment and functions of data and Safety Monitoring Committee issued by the World Health Organization, an independent Data and Safety Monitoring Boards (DSMB) will be established in this study. The committee is composed of 7 experts including clinical, social researchers, biostatistics, and other relevant personnel outside the research team, and will be responsible for the data evaluation during the study period, and will be responsible for the important data questions; the safety data report shall be consulted and monitored. In the study of this project, DSMB conducts safety assessment on the accumulated data of the clinical study to ensure the safety of the participants, monitor the implementation of the study, including the enrollment, protocol violation and dropout of the overall and each center, baseline characteristics, accuracy, completeness and timeliness of the monitoring data, and monitor the compliance of the researchers and participants with the protocol.

The research group shall report the serious AE report judged by the investigator to be possibly related or related to the research intervention to the DSMB chairman by telephone or email, and submit the formal written report. All other AEs and serious AE reports shall be summarized and submitted to the DSMB chairman (every month). Relevant analysis reports include but are not limited to the following: list of serious AEs, AEs, violations or deviations from the protocol, research progress report, list of dropped participants, etc. After DSMB reviews the data, it can suggest to continue as planned, continue or terminate the trial after modifying the protocol, or suspend the study until more supporting information is available.

### 2.12. Informed consent

Before each participant is enrolled in this study, the investigator has the responsibility to fully and comprehensively introduce the purpose, procedure, and possible risks of this study to them in written form. Participants should be informed that they have the right to withdraw from the study at any time, and each patient must be given an informed consent notice sheet before enrollment. The investigator is responsible for ensuring that each participant signs the informed consent before entering the study and keeps it in the study file. The personal information about potential and enrolled participants will be protected confidentiality before, during, and after the trial.

## 3. Discussion

This paper describes the protocol of a multicenter, prospective, registry-based observational registry study to monitor the efficacy and safety of the TCM BDT for FC. BDT is a functional food for Chinese herbal tea bags, which has a laxative effect and has been commonly used among people with constipation for more than 20 years in China. In particular, the active ingredients of BDT, such as total anthraquinones, sennoside A, sennoside B, and rhein, are the main compounds of BDT in the treatment of constipation. Previous studies have demonstrated that anthraquinone, especially its dianthrone compounds, such as sennoside A and sennoside B, exert significant laxative effects in promoting gastrointestinal motility and relieving FC.^[14]^

There are a large number of TCM health foods in China, but the guiding principles for the use of TCM health foods are currently lacking. In order to maximize the effect of TCM health foods on the importance of the application of TCM syndrome differentiation to health products, we put the standard of syndrome differentiation into the design of this study. As we know, TCM has its own properties (such as hot or cold), and it is theoretically believed that BDT has a better effect on constipation patients with dryness-heat syndrome. We aimed to identify the most suitable syndrome or clinical manifestation of BDT in this study.

This study is the first registry-based study to collect real-world data of participants diagnosed with FC receiving BDT treatment in community hospitals. The results of this registry may demonstrate the acceptance of BDT in patients and evaluate the effectiveness and safety of BDT for FC. Second, the long-term effect of BDT on FC was evaluated by observing the time the participants used the laxative product within 2 weeks of the end of the trial. Furthermore, the laxative effect of BDT on people with different syndromes (dryness-heat syndrome and non-dryness-heat syndrome) was investigated. The factors that affect the efficacy of BDT are analyzed by multiple factors, such as the severity of constipation, age, sex, occupation, and medical history. Finally, we evaluate the economic value of BDT. This is the first study to evaluate the effectiveness of TCM health products that are already on the market for people with different syndromes. This study has great significance.

In an open clinical study, quality control has become an important aspect worthy of attention in the process of implementation, and the concept of quality control should be implemented in every process of the study.^[15]^ For example, the method of continuous selection should be adopted to reduce the selection bias in the selection of participants. Clinical research should be strictly controlled for data collection, management, and analyses. We can carry out training for clinicians and research coordinators who collect data, make full use of the Internet, and establish a research website. The clinical diagnoses, relevant variables, and results of all participants were standardized to minimize the error of the collected data. The central database can be established, the regularly uploaded data should be manually checked, and existing problems need to be fed back to researchers immediately. This research will be more valuable with strict quality control.

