### 2.4. Recruitment

Participants will be recruited from 3 comprehensive hospitals and 15 primary medical institutions across China. We will also advertise through websites and post recruitment posters on the walls of the entrance of each clinic to encourage voluntary participation in this study. If the participants met the inclusion criteria in this study, the researcher will fully explain the aim of this study and details of the procedures, including research usage, confidentiality, and provision of data to third parties for analysis, and will obtain informed consent from the potential participants. Simultaneously, professional clinicians will be arranged to observe the status of the participants and provide medical assistance.

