### 2.5. Exposure

The participants will receive treatment with BDT (Beijing Aote Shuer Health Care Product Development Co. Ltd, Lot Number: 01200703, Beijing, China) twice a day (1 hour after lunch and 1 hour after dinner). The specification of tea is 2.5g/bag, and it is brewed once with 150 to 250 mL of boiling water. Health food and drugs (including dietary fiber and probiotics) with laxative effects shall not be taken orally and externally 4 weeks before the trial and during the trail, which will affect the judgment of the results.

During the experiment, the diet, drinking water, exercise, and rest were basically the same as before. If the constipation is aggravated, it is recommended that the participant go to the hospital for physical examination and use other laxative drugs. In case of serious adverse reactions, the participant shall immediately stop taking this product and seek medical treatment in time. The trial unit will bear the treatment costs and corresponding compensation arising therefrom.

The compliance of the participants was monitored by the counting method of the test products. Compliance = (actual dose/expected dose) × 100%.

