### 2.6. Outcomes measures

Researchers determined that the following data will be collected to observe the efficacy and safety of the TCM BDT for FC. The detailed research schedule for this registry study is presented in Table 1.

**Table 1 T1:** Research schedule of the registry study.

	Enrollment baseline	Subsequent visits	End of treatment	Subsequent visits
		The 7th day		The 14th day after the end
Informed consent	√			
Eligibility screening	√			
Matters needing attention	√			
Demographic characteristics	√			
Physical examination form	√	√	√	√
Bowel movement dairy (everyday)	√	√	√	√
PAC-SYM	√	√	√	√
PAC-QOL	√	√	√	√
TCM Syndrome Scale*	√	√	√	√
Economic questionnaire			√	
AEs		√	√	√

Note: the time window is specified as 5 days.

AE = adverse events, PAC-QOL = Patient Assessment of Constipation Quality of Life questionnaire, PAC-SYM = Patient Assessment of Constipation Symptoms questionnaire, TCM = traditional Chinese medicine.

* Only for people with dryness-heat syndrome.

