### 2.8. Sample size calculation

We plan to recruit at least 1000 patients during the study period. Empirically considering the trends of patients visiting each community hospital, we estimated that approximately 1000 participants will be enrolled (100 patients or more per year per clinic) for a year. The study started in July 2022, is currently ongoing, and will finish in July 2023.

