### 2.9. Statistical analysis plan

All statistical analyses were conducted using two-tailed tests and the significance level was set at 5%. An analysis of covariance will be performed when it is necessary to control for underlying variables, such as demographic variables. The propensity score can effectively balance the distribution and composition of each characteristic variable between groups and evaluate the relationship or role between intervention measures and outcome variables. It is often used to control for confounding bias among non-randomized groups in observational studies. The generalized estimating equation has obvious advantages over other methods for evaluating propensity score values and is the most recommended algorithm among the current evaluation methods for propensity score values.^[13]^ The mean of other scoring data will be analyzed using the *t* test or the chi-square test. The incidence of AEs within the groups was also evaluated using the chi-squared test. For missing data, the last observation carried forward will be used through a case report form inspection to replace the missing value. All statistical analyses in this study were conducted using SPSS 20.0 (SPSS Inc., IBM Corp., Armonk, NY).

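### Severity of constipation is planned as a factor affecting BDT efficacy, but there is no comparator and, if severity is the outcome's own baseline score, its coefficient will be significant almost always even when the benefit is identical at every severity

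*Protocol article*

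**What the plan says.** The Discussion (section 3) describes a multi-factor analysis: "The factors that affect the efficacy of BDT are analyzed by multiple factors, such as the severity of constipation, age, sex, occupation, and medical history". The same section gives the purpose: "We aimed to identify the most suitable syndrome or clinical manifestation of BDT in this study".

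Section 2.5 gives one exposure for all: "The participants will receive treatment with BDT". Section 2.1 forms groups only by TCM syndrome at entry, not by treatment.

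Table 1 (section 2.6) schedules PAC-SYM, PAC-QOL and the diary, listed as "Bowel movement dairy (everyday"), at baseline and at every later visit. It lists no separate severity instrument. The TCM syndrome scale is also repeated, but it serves to classify dryness-heat syndrome.

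Section 2.9 sets the test level: "All statistical analyses were conducted using two-tailed tests and the significance level was set at 5"%. It offers analysis of covariance where underlying variables need control, with demographic variables as the example, and does not name the baseline score. Section 2.8 sets the size: "We plan to recruit at least 1000 patients during the study period".

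The article does not say how severity is measured, which outcome counts as efficacy in this analysis, or whether efficacy is a change, a final value or a response.

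**The concern.** To say that severity affects the efficacy of BDT is to say that the benefit differs between mild and severe constipation. A regression of outcome on severity in treated patients alone tests something else: whether the slope on severity is zero. Without an untreated or comparator course at each severity, that slope mixes three things: a different effect of BDT, regression to the mean, and severity simply predicting the later score.

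If severity is the starting value of the outcome score, the slope is generally non-zero even when the benefit is the same for everyone. Baseline is part of the change score, and baseline correlates with the final score. At this sample size such a slope will nearly always reach significance. Its meaning then depends on the coding: the same data suggest that BDT suits severe patients (change) or mild patients (final score). Because the stated aim is to find whom the product suits, such a result could be reported as guidance on who should use it.

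This is separate from confounding between the dryness-heat and other participants. Balancing or adjusting the syndrome groups does not remove it.

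**Working it through.** **Inputs from the article.** n = 1000 (section 2.8); two-sided 5% (section 2.9); no comparator (section 2.5); the same instruments at baseline and follow-up (Table 1).

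**The plan's own figure.** The article gives no effect size, SD or power for this analysis, so there is nothing to reproduce for it. The 1000 rests on a recruitment rate: "we estimated that approximately 1000 participants will be enrolled (100 patients or more per year per clinic) for a year". At 100 per clinic that is 100 × 15 = 1500 or 100 × 18 = 1800, while 1000 corresponds to 10 clinics. This is a separate matter; 1000 is used here only as n.

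**Assumptions not in the article.** Baseline score Y0 and follow-up score Y1, higher meaning worse (as the article states for PAC-QOL); equal SDs; correlation r between visits; one constant benefit d for everyone, so severity truly does not alter the effect.

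**Step 1: change score.** Improvement is Y0 − Y1. In units of the common SD, cov(Y0, Y0 − Y1) = 1 − r and var(Y0 − Y1) = 2(1 − r). So corr(Y0, improvement) = (1 − r)/√(2(1 − r)) = √((1 − r)/2). The constant d drops out.

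**Step 2: rejection rate.** By Fisher's z, the test statistic is centred on atanh(corr) × √(n − 3), with √997 = 31.58, against 1.96. For example, r = 0.95 gives √0.025 = 0.158, atanh = 0.159, and 0.159 × 31.58 ≈ 5.03. Since 5.03 − 1.96 = 3.07, the rate is 99.9%.

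| r | corr(baseline, improvement) | Rejection, change score | Rejection, final score (corr = r) |
|---|---|---|---|
| 0.1 | 0.671 | 100% | 89% |
| 0.2 | 0.632 | 100% | 100% |
| 0.5 | 0.500 | 100% | 100% |
| 0.7 | 0.387 | 100% | 100% |
| 0.9 | 0.224 | 100% | 100% |
| 0.95 | 0.158 | 99.9% | 100% |
| 0.98 | 0.100 | 89% | 100% |
| 0.99 | 0.071 | 61% | 100% |

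The nominal rate is 5%. With n = 200, the change-score rate is 99.99% at r = 0.7 and 89% at r = 0.9.

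**Step 3: direction.** The slope of improvement on baseline is 1 − r (severe patients improve more). The slope of final score on baseline is r (severe patients end worse). Both are positive for 0 < r < 1, with opposite clinical meaning.

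**Step 4: apparent size.** For normal scores split at the baseline median, the halves differ at baseline by 2 × 0.798 = 1.596 SD, so their improvement differs by 1.596 × (1 − r): 0.96, 0.64 and 0.32 SD at r = 0.4, 0.6 and 0.8, with no true difference in benefit.

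**Step 5: unequal SDs.** With follow-up SD = k × baseline SD, the correlation of Y1 − Y0 with baseline is (rk − 1)/√(1 + k² − 2rk). At r = 0.8 this is −0.316 for k = 1 and −0.179 for k = 1.1 (both 100% rejection), and 0 for k = 1.25. At k = 1/r the rate returns to 5%.

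**Step 6: simulation.** In 1000 runs with n = 1000 and between-visit correlation 0.5 to 0.9, change, final score, absolute response and response defined by change all gave 99.9% to 100%. Change with 20% of follow-up values replaced by baseline gave 99.8% to 100%. With severity taken from a separate measure that shares no error with the score, change and change-based response gave 4% to 6%, but final score and absolute response still gave 100%.

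**The case against.** The strongest objection is that the article never defines severity. It could be graded from the Rome IV symptoms at screening or from medical history. A pre-treatment diary value is not secure either: the text of section 2.6 places the diary in the treatment period, while Table 1 ticks it at baseline. The planned analysis appears in one Discussion sentence of a condensed article, and the definition of severity and the coding of efficacy may sit in a fuller document. In a single-arm registry, factors affecting efficacy can also be read as predictors of outcome, which is a legitimate prognostic question.

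Much of this stands. A reader might infer that severity is by definition the baseline of the same scores and that its test is certain to be significant whatever BDT does. The documents do not support that. The identity is an inference, though a natural one given Table 1. The rate drops to 89% at r = 0.98, returns to 5% when the follow-up SD equals baseline SD/r, and is about 5% for a separately measured severity tested against change. Time to laxative re-use has no baseline value, so the formula does not reach it; severity could still predict re-use there without altering BDT's effect. Nor does the direction depend only on change versus final score, since other codings such as percentage change are possible.

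What does not stand is that the matter is only an omitted detail. The article states both the analysis and an effect-type reading, alongside an aim of finding whom BDT suits. No later definition of severity supplies the missing comparator. That limit on interpretation applies equally to age, sex, occupation and medical history; what is particular to severity is the built-in association with the score.

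**Conclusion.** The concern holds in conditional form. With no comparator, a severity coefficient cannot be read as showing that severity alters the effect of BDT, however severity is defined. If severity is the baseline of the outcome score, significance is close to assured at n = 1000 under an identical benefit for all: 99.9% or more for change scores at r = 0.1 to 0.95, and about 100% for final scores at r of 0.2 or more, against a nominal 5%. This rests on equal SDs and an assumed r. It weakens for change scores as r approaches 1 or as the follow-up SD rises towards baseline SD/r, and it does not extend to time to laxative re-use. The point should be corrected because it governs what the study may conclude about whom the product suits.

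**What to change.** In the Discussion sentence on factors, state that:

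- the baseline score enters the multi-factor model as an adjustment covariate, with severity defined;
- any severity result is prognostic only and will not be read as evidence that BDT works better or worse in severe constipation;
- baseline and follow-up scores by severity stratum are shown descriptively, without a test of improvement across strata.

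Removing severity altogether is more than is needed. Relating change to the mean of the two scores is not a safe substitute. In simulation it rejected in 4% to 5% of trials with an untruncated baseline, but in 100% when baseline was cut off at −0.5 SD (an assumed stand-in for the effect of the entry criteria; r = 0.4 to 0.8, 500 trials each).

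The cost is a short change of wording, with no new data or patients. The downside is giving up a claim that severity determines BDT efficacy, which this design cannot support.

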## 4. Conclusion

In conclusion, this protocol will provide details for investigators regarding BDT in health care for FC. The results of this registry may demonstrate the acceptance of BDT in patients and evaluate its effectiveness and safety.
